### Safety procedures

#### Adverse events

For the purposes of this trial, an adverse event (AE) is defined as:

- any unscheduled contact (e.g. phone calls, face-face visits etc) made by the patient, or carer to the outpatient or community treatment nurse, Investigator or member of his/her team, GP, or other support staff in relation to their current course of treatment.

- any unscheduled contact (e.g. phone calls, face-face visits etc) made by the out-patient, or community treatment nurse to the Investigator or member of his/her team, GP, or other support staff relating to the management of the patient receiving treatment.

To ensure accurate collection of trial-specific AEs, trial patients and treatment delivery nurses are issued with a purpose-designed diary in which to record all occasions when unscheduled contact is made. Specific information regarding contact is also requested. All AEs which occur from randomisation until the final trial visit are recorded. Specific information to be recorded in the diary regarding AEs includes the date and time of occurrence, main reason for making contact, with whom contact is made and outcome.

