### Study duration

The study period is defined as being 12 weeks on a particular course of treatment. Where patients continue treatment beyond 12 weeks, those being treated at home can continue to do so. However, if they prefer to be treated in hospital they can transfer. Those patients randomised to hospital treatment cannot cross over to treatment in the community, since community-based treatment is not standard practice locally. Patients stopping treatment earlier than 12 weeks are not replaced in the study, but the reason for stopping is noted. They are included for the collection of study outcomes at 12 weeks, since analysis is on an intention-to-treat basis.

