### Patient assessments

Blood tests, radiological investigations and clinician reviews are undertaken on patients in all arms of the study, as per standard practice defined for each disease site and treatment regimen being used. Patients receiving treatment in the community have blood taken in the community and sent to the hospital laboratory so that the result is available to the Investigator on the day that treatment is due.

Prior to each course of treatment, patients receiving treatment in hospital are seen by the Investigator or delegated team member as per standard clinical practice, before proceeding with treatment. Patients receiving treatment in the community are assessed by the community chemotherapy nurse, who liaises with the prescribing clinician before proceeding with each course of treatment. Patients on any arm of the study can be referred for non-routine clinical review on request by another health care professional or on request by the patient. The frequency and reasons for extra clinical reviews will be monitored as part of the study, as part of adverse event reporting.

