###### iv) *Patient safety*

CUH and WSH have in place a comprehensive set of policies and procedures governing community-based care. Specifically for cancer, the Cancer Treatment in the Community (CTC) policy identifies low risk patients and low risk treatments usually offered to patients in the hospital out-patient and day unit facilities which are potentially suitable for delivery in the community (Table 1). In addition, the CTC policy describes a clinical governance framework for ensuring patient safety in the community, reflecting standard policies and procedures adhered to when delivering cancer treatment in hospital. To be considered for this trial, both the patients and the treatment being offered are required to meet the criteria listed in the CTC Policy.

The treatments given to patients taking part in this trial are by definition those which are well established, with an excellent safety record. Our hypothesis is that patients would not be adversely affected or harmed by receiving treatment in the community. Appropriate safety measures and procedures are in place for community treatment, to provide a safe environment considered to be equivalent to the hospital setting.

Patient safety will be evaluated by recording the number of adverse and serious adverse events which occur during the study period (see safety procedures).

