### Statistical Analysis

The primary analysis time-point is 12 weeks. The primary contrast is between home and GP surgery arms combined, versus hospital arm. Binary outcomes will be analysed using logistic regression. Continuous outcomes will be analysed using linear regression adjusting for randomisation stratifiers and the pre-randomisation baseline of the outcome in order to improve precision of the estimated intervention effects. Participants with valid data at follow-up but with missing data at baseline will be retained in the analysis by using the missing indicator method [20]. For measures repeated over time, linear mixed models will be used to analyse data from all time-points together, to assess for any patterns between study arms. The level of missing data will be compared by study arm. A logistic regression model will be used to examine whether baseline factors or intermediate study measures predict dropout by 12 weeks. With sufficient 12-week data, the impact of missing data on the main outcomes will be assessed using best and worst case sensitivity analyses, using multiple imputation [21], or otherwise using the linear mixed effects model with the available 4-week and 8-week data to model the 12-week effect from the trend in the outcome over time in each arm. Further analyses will include comparisons between pairs of arms, analyses at time-points and subgroup analyses, with subgroups defined by treatment intent and hospital.

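### Transfer to hospital counts as withdrawal and can end adverse-event recording early in the community arms only, against the protocol's own 12-week intention-to-treat follow-up

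*Protocol article*

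**What the plan says.** Patient safety is a secondary aim, measured by the number of adverse and serious adverse events (protocol article, Secondary Aims).

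- **Outcome window.** Section iv) Patient safety evaluates the number of "adverse and serious adverse events which occur during the study period". Study duration fixes that period: "The study period is defined as being 12 weeks on a particular course of treatment".
- **Recording window.** Adverse events states: "All AEs which occur from randomisation until the final trial visit are recorded". Serious adverse events uses the same start and end.
- **Final visit.** Study interventions places the completion visit at 12 weeks, or sooner on early withdrawal. It adds a review at the end of treatment or 24 weeks for those who continue.
- **Transfer.** Recording and collection of data makes a move from community to hospital both a serious adverse event and a withdrawal from the trial. It bars moves in the other direction. Study interventions lists problematic drug toxicity, a serious adverse event, patient request and clinical judgement as reasons.
- **Early stoppers.** Study duration keeps patients who stop treatment before 12 weeks in outcome collection at 12 weeks, on intention-to-treat grounds.
- **What is counted.** An adverse event is either "any unscheduled contact (e.g. phone calls, face-face visits etc) made by the patient, or carer to the outpatient or community treatment nurse" (or to other staff), or an unscheduled contact "made by the out-patient, or community treatment nurse to the Investigator or member of his/her team, GP, or other support staff". Patients and nurses record these in diaries with date, time, reason, person contacted and outcome.

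**The concern.** The outcome is a number of events, so its value depends directly on how long each patient is observed. Read together, the sections on transfer, completion visit and event recording give community patients a way out of observation that hospital patients do not have. Two of the listed reasons for taking it, toxicity and a serious adverse event, are closely tied to the outcome itself. A community patient with mounting problems may stop contributing events at transfer, while a hospital patient with the same problems goes on contributing to week 12.

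At stake is the credibility of the safety comparison. The expected error for unscheduled contacts, and for clinical serious events other than the transfer itself, favours community care, which is the service under test.

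A smaller matter concerns what is counted. One episode in which a patient calls a nurse, who then calls the clinician, meets both parts of the adverse-event definition and can enter the total twice.

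**Working it through.** **1. The passages side by side**

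| Section | What it implies for the end of event counting |
|---|---|
| iv) Patient safety, with Study duration | 12 weeks on treatment, all arms |
| Adverse events; Serious adverse events | final trial visit, which varies by patient |
| Study interventions | completion visit at week 12, sooner on early withdrawal |
| Recording and collection of data | transfer is withdrawal; possible from home or GP surgery only |
| Study duration | even patients who stop treatment stay in outcome collection at 12 weeks |

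The second to fourth rows shorten the window at transfer. The first and last do not. A transferred patient is still being treated, so there is less reason to lose that patient than one who has stopped treatment altogether. The sections cannot all be followed as they stand.

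**2. The plan's own figures**

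The protocol gives no event rate, transfer rate or power for safety, so there is no stated safety figure to reproduce. Its sample size concerns the QLQ-C30 score and does reproduce: 91 per arm for a 10-point difference with SD 24, and 91 / 0.70 = 130. It does not bear on this point.

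**3. Illustration A: transfer unrelated to risk**

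Assumptions: equal weekly contact rate in all arms; a proportion q of community patients transfers, uniformly over weeks 0 to 12; counting stops at transfer. The mean window lost per transferred patient is 6 weeks.

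Ratio of expected counts, community to hospital = (12 − 6q) / 12

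- q = 0.10: 11.4 / 12 = 0.95
- q = 0.20: 10.8 / 12 = 0.90
- q = 0.30: 10.2 / 12 = 0.85

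In a simulation of 130 hospital and 260 community patients (0.25 contacts per week, gamma overdispersion 1, no true difference, 2000 runs), a linear comparison of raw counts at the nominal 5% level was significant in 7%, 13% and 26% of runs. With no transfers the figure was 5%. Dividing by person-time restored a ratio of 1.00 and about 5%.

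**4. Illustration B: transfer follows risk**

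Assumptions: each patient's contact rate is proportional to a propensity g, gamma with mean 1 and variance 1; the transfer hazard is h·g. Then:

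- proportion transferring by week 12: q = 1 − 1 / (1 + 12h), so 12h = q / (1 − q)
- raw-count ratio = 1 / (1 + 12h) = 1 − q
- mean fraction of the 12 weeks observed = ln(1 + 12h) / 12h
- ratio of rates per person-time = raw-count ratio / fraction observed

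| q | 12h | Raw-count ratio | Fraction observed | Rate ratio |
|---|---|---|---|---|
| 0.10 | 0.111 | 0.90 | 0.948 | 0.95 |
| 0.20 | 0.250 | 0.80 | 0.893 | 0.90 |
| 0.30 | 0.429 | 0.70 | 0.832 | 0.84 |

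A large simulation gave the same values. When transfer depends on risk, a person-time denominator removes only part of the bias. Continued recording after transfer is what removes it.

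**5. Serious adverse events**

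The window is the same, so clinical serious events after transfer are lost in the same way. Each transfer is itself a serious adverse event, however, and only community patients can have that one. Total serious events are therefore pushed up by the criterion and down by the lost follow-up, and the net direction is not determined.

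**The case against.** The best defence is that recording and evaluation are different things. Events may be recorded to the final visit and yet be evaluated only over the 12-week study period, and collecting more than is analysed is no contradiction. The 24-week point is optional and outside the study period. The lag of up to 28 days from randomisation to treatment applies to every arm. All of that stands, and it answers any worry about windows that run too long. It does not answer the window that stops too soon: events not recorded after transfer cannot be evaluated later.

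A reader might be tempted to go further in four ways that the document does not support.

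- **That the adverse-event definition depends on venue.** It names out-patient and community nurses alike and requires the contact to be unscheduled. The sentence "Patients receiving treatment in the community are assessed by the community chemotherapy nurse, who liaises with the prescribing clinician before proceeding" describes a planned step before each course, so on its face it is not an unscheduled contact. The criterion tied to venue is in the serious adverse event list.
- **That the stated models do not suit counts.** The article says "Binary outcomes will be analysed using logistic regression" and assigns linear regression to continuous outcomes. It assigns no model to event counts, which may properly be left to the analysis plan. In the simulation, a linear comparison held about 5% when windows were equal.
- **That the result cannot be read as safety at all.** Deaths, unplanned hospitalisation and grade 3 or 4 toxicity are captured separately, and dated diary entries permit a common window.
- **That individual windows differ by some large multiple.** The document gives no minimum time to transfer, and the longest window needs the optional 24-week point to count as the final visit.

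**Conclusion.** The point holds for the event window. As written, transfer can end event recording in the community arms only, for reasons linked to the outcome, and this conflicts with the 12-week study period and the intention-to-treat follow-up that the same document sets out.

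The expected effect is to lower community counts of unscheduled contacts, and of clinical serious events other than transfer, with no true difference. Its size cannot be determined from the document. The illustrative raw-count ratios are 0.95 to 0.85 if transfer is unrelated to risk and 0.90 to 0.70 if it follows risk, for assumed transfer proportions of 10% to 30%. If transfers prove rare, or if sites in practice keep recording to week 12, the bias is small or absent.

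This concerns a stated secondary outcome, not the primary one. It should be corrected, but it does not undermine the trial's main comparison.

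**What to change.** Reconcile the sections on transfer, adverse events and serious adverse events with Study duration and iv) Patient safety, as follows.

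1. Use one window for the between-arm comparison: from randomisation (or from first study treatment, if preferred) to week 12 for every patient, whether or not treatment moves to hospital.
2. State that adverse and serious adverse event recording continues after transfer, so that a change of venue does not end data collection.
3. Report events after week 12 separately.
4. Describe the adverse-event count as unscheduled contacts, distinct from clinical serious adverse events, and report patient- or carer-initiated contacts separately from nurse-to-clinician contacts, so that one episode is not added to a single total twice.

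The cost is small but is more than wording. Transferred patients and their nurses must go on completing diaries, and the rule that equates transfer with withdrawal has to be amended as far as data collection is concerned. The diaries already carry dates, reasons and the person contacted, and transferred patients continue treatment in hospital, where they can be followed. Some late contacts leave the main comparison.

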#### Serious adverse events

For the purposes of this trial, a serious adverse event (SAE) was defined as including any event which:

- results in death, regardless of cause.

- is life-threatening (immediate risk of death).

- requires hospitalisation or prolongation of existing hospitalisation, excluding those planned for cancer treatment, disease related procedures, or placement of an indwelling catheter, unless associated with other serious events.

- results in persistent or significant disability/incapacity.

- consists of a congenital abnormality of birth defect.

- involves grade 3 or 4 (severe or life threatening) drug-related toxicities.

- results in the patient's treatment being switched from the community to hospital-based treatment.

This trial is not evaluating treatment *per se*, but the venue of treatment delivery. Thus, reporting of drug-related AEs is limited to reporting of severe or life threatening toxicities, according to National Cancer Institute, Common Toxicity Criteria.

All SAEs which occur from randomisation until the final trial visit are recorded. All SAEs are reported to the CCTC immediately, by completing an SAE form, and assessed by the Chief Investigator. Autopsy data, where available, for deaths occurring from randomisation until 28 days after the last planned treatment administration are provided to the CCTC.

The relationship of SAEs to treatment delivery venue is assessed using the following definitions:

- Not related - The adverse event would definitely have occurred whatever the venue

- Unlikely to be related - The adverse event would probably have occurred whatever the venue

- Possibly related - The adverse event had a timely relationship to treatment venue. However, a potential alternative aetiology existed.

- Probably related - The adverse event had a timely relationship to treatment venue and a potential alternative aetiology was not apparent.

- Definitely related - The adverse event had a timely relationship to treatment venue and a potential alternative aetiology was not apparent. Upon switching treatment to hospital-based delivery, the adverse event would definitely not occur.

'Unlikely' and 'Not related' are considered not treatment venue related. 'Definitely', 'Probably' and 'Possibly' are considered treatment venue related.

In the case of an SAE, the subject will be followed up until recovery or stabilisation. The Investigator will take all measures necessary to resolve any SAE.

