### Recording and collection of data

Upon randomisation of an individual patient, a pack containing specifically designed data collection forms, questionnaires and diaries is provided to the Investigator. The forms allow collection of essential information required for the study at each predefined trial data collection point. The study has four mandatory and 1 optional data collection point. Mandatory data collection points are baseline (at the start of study treatment), then approximately 4 weeks, 8 weeks and 12 weeks after commencing treatment. For patients continuing treatment beyond 12 weeks, there is an optional data collection point at 24 weeks or on stopping treatment, whichever occurs sooner. The baseline, 12 week and 24 week data collection visits take place at hospital. On these occasions, study forms will be completed by the Investigator or a member of his/her team, which may include a specialist or research nurse/practitioner. Patient questionnaires and diaries are given to the patient and/or collected from the patient as appropriate at these visits.

In order to allow for different treatment schedules, the second and third data collection points may be flexible to within 1 week either side of the planned 4 and 8 week time points. For patients having treatment in hospital, on these occasions, forms are completed by the Investigator or a member of his/her team, which may include a specialist or research nurse/practitioner. Patient questionnaires are given to and collected from the patient as appropriate at these visits. For patients having treatment in the community, these study forms are completed by the community chemotherapy nurse. Patient questionnaires are given to and collected from the patient as appropriate at these visits.

Following each planned data collection point, study forms and questionnaires are returned to the Outreach Trial Coordinator, who is responsible for creating and completing the unique patient Case Report Forms (CRF).

Patients randomised to receive treatment in either community setting may be transferred at any time to continue treatment in hospital, and the date and reason for transfer will be documented. Transfer of care to the hospital constitutes a serious adverse event (SAE) and withdrawal from the trial. Patients randomised to receive treatment in hospital may not be transferred to either location in the community, since this is not standard clinical practice locally.

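### Counting every community-to-hospital switch as an SAE, which the hospital arm can never incur, biases the between-arm SAE comparison against community delivery

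*Protocol article*

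**What the plan says.** All references are to the protocol article.

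- **Definition.** *Serious adverse events* lists, beside the usual criteria, an event that leads to the patient's "treatment being switched from the community to hospital-based treatment". *Recording and collection of data* is broader and names the transfer itself: "Transfer of care to the hospital constitutes a serious adverse event (SAE) and withdrawal from the trial".
- **Reasons for transfer.** *Study interventions* allows community treatment to be moved to hospital for problematic toxicity or an SAE. It also allows this at the patient's own wish, or on the Investigator's judgement after discussion with the community nurse.
- **No reverse move.** *Recording and collection of data* states: "Patients randomised to receive treatment in hospital may not be transferred to either location in the community". *Study duration* says the same: "Those patients randomised to hospital treatment cannot cross over to treatment in the community".
- **Use of the count.** *Secondary Aims* makes the number of adverse and serious adverse events the measure of safety, and *iv) Patient safety* repeats it: "Patient safety will be evaluated by recording the number of adverse and serious adverse events which occur during the study period". That section also states the hypothesis that community delivery does no harm.
- **Monitoring.** Under *Trial organisation and management*, the independent data and safety monitoring committee (IDSMC) follows SAEs and may advise on amending or ending the study for safety reasons.

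Nowhere are switch events taken out of the SAE count.

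**The concern.** An SAE count compares arms fairly only if a patient with the same clinical course would be counted the same way in each arm. Here that fails. A patient treated at home who is clinically well but asks to go back to the day unit has an SAE. A patient in the hospital arm who is equally dissatisfied has no event that this criterion could record.

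At stake is a secondary outcome, but one that commissioners would read closely. The trial hypothesises that community delivery is not harmful, and the outcome meant to examine this has a component that can move in one direction only. The IDSMC sees the same SAEs during the trial.

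**Working it through.** **1. Can each arm meet each criterion?**

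| SAE criterion | Hospital (A) | Home (B) | GP surgery (C) |
|---|---|---|---|
| Death | yes | yes | yes |
| Life-threatening event | yes | yes | yes |
| Unplanned or prolonged hospitalisation | yes | yes | yes |
| Disability | yes | yes | yes |
| Congenital abnormality | yes | yes | yes |
| Grade 3–4 drug-related toxicity | yes | yes | yes |
| Switch from community to hospital | **no** | yes | yes |

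Only the last row differs by arm.

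**2. Arm sizes, checked against the plan's own calculation.** *Sample size* gives 130 per arm, a 10-point difference, SD 24, 5% significance, 80% power and 30% loss.

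- Evaluable per arm: 2 × (1.960 + 0.842)² × 24² / 10² = 90.4, so 91.
- Inflated for loss: 91 / (1 − 0.30) = 130. This reproduces.
- Power with 91 against 91 is 80.3%. With 91 against 182 it is 90.1%. Both agree with the stated 80% and 90%.

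The safety comparison of the combined community arms with hospital is therefore 260 against 130 randomised patients.

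**3. Model for the artificial excess.** The documents give neither rate, so both are assumptions:

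- *b*: proportion of patients with an SAE on the shared criteria, equal in all arms (no true difference in harm);
- *s*: proportion of otherwise SAE-free community patients who switch.

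Hospital proportion = *b*. Community proportion = *b* + (1 − *b*)*s*. The excess is (1 − *b*)*s*, which is zero only when *s* = 0.

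The chance of a significant excess, for a two-sided 5% test of two proportions, is Φ[(*d* − 1.96 × SE₀) / SE₁]. Here *d* is the excess, SE₀ the pooled and SE₁ the unpooled standard error.

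Worked case, *b* = 0.20 and *s* = 0.10:

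- Community proportion = 0.20 + 0.80 × 0.10 = 0.28, so *d* = 0.08. That is 260 × 0.08 = 20.8 extra community patients with an SAE.
- Pooled proportion = (130 × 0.20 + 260 × 0.28) / 390 = 0.2533.
- SE₀ = √[0.2533 × 0.7467 × (1/130 + 1/260)] = 0.0467.
- SE₁ = √[0.20 × 0.80/130 + 0.28 × 0.72/260] = 0.0448.
- Φ[(0.08 − 1.96 × 0.0467) / 0.0448] = Φ(−0.26) = 0.40.

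**4. Range.**

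| *b* | *s* | Community vs hospital | Risk ratio | Chance of false excess |
|---|---|---|---|---|
| 10% | 2% | 11.8% vs 10% | 1.18 | 7% |
| 10% | 5% | 14.5% vs 10% | 1.45 | 23% |
| 10% | 10% | 19.0% vs 10% | 1.90 | 64% |
| 10% | 20% | 28.0% vs 10% | 2.80 | 99% |
| 20% | 2% | 21.6% vs 20% | 1.08 | 5% |
| 20% | 5% | 24.0% vs 20% | 1.20 | 14% |
| 20% | 10% | 28.0% vs 20% | 1.40 | 40% |
| 20% | 20% | 36.0% vs 20% | 1.80 | 91% |
| 30% | 2% | 31.4% vs 30% | 1.05 | 5% |
| 30% | 5% | 33.5% vs 30% | 1.12 | 10% |
| 30% | 10% | 37.0% vs 30% | 1.23 | 27% |
| 30% | 20% | 44.0% vs 30% | 1.47 | 77% |

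The reference value is 2.5%, the chance of a false result in this direction with a fair definition. With the switch criterion left out of the comparison and equal harm, the risk ratio returns to 1.00 and the chance to 2.5%.

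**The case against.** The best defence is that flagging a switch for immediate report is a sensible trial-specific choice when venue is the intervention. The outcome is secondary, the primary end point and sample size are untouched, no numerical SAE stopping boundary is stated, and tables by criterion may sit in an analysis plan that is not shown. The bias also runs against the trial's own hypothesis. Most of this stands and limits the severity. It does not remove the point: the definition and the outcome built on it are both written here, and nothing in the text excludes switches from the count.

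A reader might also infer more than the documents support:

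- **That an excess is certain.** It arises only from switches that meet no other SAE criterion. A switch after a grade 3–4 toxicity or an unplanned admission would have counted in any arm.
- **That real harm can no longer be told from a change of venue.** The date and reason for each transfer are documented and every SAE has its own form, so the two can be separated from recorded data.
- **That one admission leading to a transfer counts twice.** An SAE is defined as any event meeting a listed criterion. No rule counts per criterion.
- **That *Study duration* shows preference switches entering the 12-week comparison.** The sentence "However, if they prefer to be treated in hospital they can transfer" concerns treatment continuing beyond 12 weeks. The support for preference switches during the study period is in *Study interventions*.
- **That the relatedness scale adds a second bias.** The top grade does require that "Upon switching treatment to hospital-based delivery, the adverse event would definitely not occur", which fits a hospital patient poorly. But *Probably* and *Possibly related* fall in the same venue-related group, so the related/not-related split need not change.

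The relatedness grading does not repair the count either, because it classifies SAEs that have already been counted. Finally, transfer is also called a withdrawal from the trial. If that ended event recording, later SAEs in switched patients would be lost and would partly offset the bias. That would be a second distortion, not a safeguard.

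**Conclusion.** The concern holds in this form: as written, the SAE count is biased against the home and GP surgery arms whenever a community patient switches without meeting another SAE criterion. The direction follows from the text alone. The size does not, because the protocol states no SAE rate and no switch rate. It is modest if such switches are rare (about 5–7% chance of a false excess at 2% switching, against 2.5%) and large if they are common (77–99% at 20%). These figures assume equal true harm, base SAE proportions of 10% to 30%, all 390 randomised patients and a patient-level test of two proportions. The protocol speaks of the number of events and names no test specific to SAEs, so they illustrate scale and are not a forecast.

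This should be fixed before any between-arm SAE comparison is made. It does not affect the validity of the primary analysis.

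**What to change.** For the between-arm safety comparison and the IDSMC tables, count only SAEs that meet a criterion open to every arm: death, life-threatening event, hospitalisation as already defined, disability, congenital abnormality, and grade 3–4 drug-related toxicity. A switch that follows such an event still counts through that event. Report all switches, with date and recorded reason, as a separate descriptive outcome for arms B and C. Immediate notification of switches to the trials centre can stay, and the rules on who may transfer need no change for this purpose.

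The cost is a short change of wording in the safety section and a split on the SAE form and in the tables. No new data are needed and the sample size is unaffected. Rewording *Definitely related* so that it reads sensibly for a hospital-arm patient is optional.
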